**Figure 1. f1:**
[figure not shown]
Study design including grouping, intervention, assessment plan and follow-up. *FES – Function Electrical Stimulation, MRP – Motor Relearning Programme, NIH – National Institutes of Health.

### Assessment criteria

The assessment criteria will be the Fugl-Meyer assessment, one-leg stance test, gait parameters (distance and time parameters), modified Ashworth scale, functional reach test, quality of life scale, Barthel index, NIH stroke scale score (NIHSS).
^
5
^
^,^
^
6
^

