## Introduction

In clinical practice, stroke has been very notorious for impeding the continuity of life and day-to-day activities. It is the most common example of such a crippling disorder. On extensive review of contemporary literature, it is observed that, despite massive worldwide efforts in this science to rectify early results in reducing the risk of death or disability, it is disappointing.
^
1
^ Partial recovery is obtained after a particularly long time. Moreover, it is observed that there are certain limitations, contra-indications, or side effects of currently established treatment modalities for stroke.
^
2
^

Considering the complicated and critical nature of the disease, i.e., stroke, it becomes imperative to search for safe, promising, and effective treatment modalities in alternative sciences for early rehabilitation purposes for stroke. Though most of the studies suggest that the individual use of
*Panchakarma* therapy, external oleation (
*Bahya Snehana*), sudation therapy (
*Swedana*) along with medicated enema (
*Basti*) and conventional physiotherapy, i.e., Motor Relearning Programme (MRP), and the combination of electrical modality with Functional Electrical Stimulation (FES) shows promising results in the rehabilitation of patients with stroke.

However, no study has been carried out to assess their combined effects on the therapeutic outcome of the rehabilitation of such patients. Moreover, the research is also required to determine the MRP and FES combined effect of supporting stroke patients for improving knee extension and gait parameters. Therefore, this study is proposed to generate clinical evidence showing excellent post-stroke recovery within a short time in restoring gross and fine movements to the maximum extent quicker.

The study aims to analyze and compare the adjuvant role of
*Dashmoola Basti* with standard treatment in stroke rehabilitation. In addition, the efficacy of physiotherapy (MRP and FES) in rehabilitating stroke patients will be assessed. The study’s goal is to assess and compare the adjuvant role of
*Dashmoola Basti* with standard control over sensorimotor function of lower extremities in stroke patients using the Fugl-Meyer assessment, as well as to assess and compare the adjuvant role of

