### Sample size

Due to practical considerations such as cost, patient inconvenience, judgments not to proceed with an investigation or a lengthy study duration, the number of participants in the study is restricted. So for the phase-I trial, 20 sample size is considered for each group.
^
3
^

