### Setting

Locus of the study: out patient department and inpatient department of Panchakarma & Kayachikitsa department, Mahatma Gandhi Ayurveda College Hospital and Research Centre (MGACH&RC), Salod (Hirapur) Wardha, Maharashtra. & Department of Neuro physiotherapy, Ravi Nair Physiotherapy College, Sawangi, Wardha Maharashtra, Datta Meghe Institute of Higher Education and Research, Wardha, Maharashtra.

Study setting: The study will be conducted in
*Panchakarma* OPD & IPD, Mahatma Gandhi Ayurveda College Hospital and Research Centre (MGACH&RC), Salod (Hirapur) Wardha, Maharashtra.

Patients will be recruited after approval from Clinical Trials Registry - India (CTRI), and the exposure period for treatment will be one month. The follow-up will be conducted on the 60
^th^ and 90
^th^ day of treatment.

Criteria for discontinuing or modifying: if patients are willing to quit in between they will be allowed to quit and will be replaced; if the patient develops an acute illness during the trial, which may hamper the study and withdrawn patients will be replaced.

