### Data collection, management, and analysis methods

For retention of patients, appointment reminders will be scheduled, and question-answering sessions will be planned. The complete follow-up will be mentioned in the patient file, and if patients are required to withdraw or discontinue, the patient file will be closed and maintained for the record purposes.

Observations will be made after the completion of the study, according to the data collected with the help of the following:
I.Case registration form with detailed history and examinationsII.Follow-up assessment proforma

The principal investigator and co-investigator will do data monitoring and coding. Data entry will be done in soft copy and case record form in hard copy. The values will be verified twice before submission in soft copy. Each file of the patient is secured with a specific patient code.

The data obtained will be calculated using the Student’s Paired ‘t’-test and Unpaired ‘t’ test for objective variables with
SPSS statistical software.

*To verify the significance of the results*

Improvements in Fugl-Meyer assessment-35%, one leg stance test-20%, functional reach test-35%, quality of life scale-25%, Barthel index-25% and NIH stroke-scale-score-20% will be considered as significant.

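### Replacing patients who quit or fall ill, with only efficacy outcomes named, would make the final 20 in Group B under-represent harm from the added regimen

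*Protocol article*

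**What the plan says.** All references are to the protocol article.

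- **Setting** (criteria for discontinuing or modifying): patients who want to quit may do so and are replaced. The rule for illness reads "if the patient develops an acute illness during the trial, which may hamper the study and withdrawn patients will be replaced". It does not separate illness related to treatment from other illness.
- **Data collection, management, and analysis methods**: when a patient withdraws or discontinues, "the patient file will be closed and maintained for the record purposes". The stated analysis is paired and unpaired t-tests.
- **Assessment criteria**: "The assessment criteria will be the Fugl-Meyer assessment, one-leg stance test, gait parameters (distance and time parameters), modified Ashworth scale", then functional reach, quality of life, Barthel index and NIHSS. **Variables to be measured** frames the outcomes as improvements on nearly the same scales, and the percentage thresholds in the data section cover efficacy scales only.
- **Interventions** and Table 1: both groups receive modern treatment and physiotherapy. Group B alone also receives massage, sudation and alternating enemas from day 1 to day 30.
- **Sample size**: "So for the phase-I trial, 20 sample size is considered for each group".
- **Introduction**: the background says "it becomes imperative to search for safe, promising, and effective treatment modalities in alternative sciences".

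**The concern.** The replacement rule acts on the patients most likely to carry a harm signal. A Group B patient who becomes acutely unwell, or who stops because the regimen is hard to tolerate, is substituted by someone else. If the results describe the 20 who remain, they describe people selected for having neither fallen ill nor quit.

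Two things are at stake. First, an apparently clean record for a 30-day added regimen could pass to the next study without support. Second, the rule applies to both arms, but only one arm is exposed to the added regimen. Regimen-related removals would therefore be one-sided, and the efficacy comparison would no longer be between the groups as randomised.

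**Working it through.** **Nothing to reproduce.** The 20 per group rests on practical limits. The article gives no alpha, power, effect size, standard deviation or dropout rate, so the check consists of reading the rules together and then an illustration.

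**The rules side by side.** Follow a Group B patient who has an acute illness related to the regimen.
1. If the illness may hamper the study, or the patient quits because of it, the Setting section has the patient replaced.
2. If that patient withdraws or discontinues, the data section closes the file. It is kept, but no section gives it a place in the analysis.
3. If the patient stays in, neurological worsening could appear on NIHSS, Barthel index or Fugl-Meyer. A harm that does not affect function or stroke severity has no scale of its own among the stated outcomes.

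**Illustration.** Inputs: n = 20 (Sample size), and an assumed risk p of a harm event in Group B of 5%, 10% or 20%. These rates are not in the document.

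*If the first 20 starters are all counted:* P(at least one event) = 1 − (1 − p)^20.
- p = 0.05: 1 − 0.95^20 = 0.642, or 64%
- p = 0.10: 1 − 0.90^20 = 0.878, or 88%
- p = 0.20: 1 − 0.80^20 = 0.988, or 99%

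If none of 20 has an event, the exact (Clopper-Pearson) two-sided 95% upper limit is 1 − 0.025^(1/20) = 0.168, or 16.8%.

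*If every event leads to replacement:* the expected number of starters needed to fill 20 places is 20/(1 − p), and the expected number removed is 20p/(1 − p).

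| Assumed p | Starters | Removed | Events in final 20 |
|---|---|---|---|
| 5% | 21.1 | 1.1 | 0 |
| 10% | 22.2 | 2.2 | 0 |
| 20% | 25.0 | 5.0 | 0 |

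The 16.8% limit relies on a zero count being improbable when p is large: (1 − p)^20 is 36%, 12% and 1% at these three rates. Under full replacement the final 20 contains no events at any p, so a zero there says nothing about p.

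*If only a fraction f of events leads to replacement:* the rate in the final set is p(1 − f)/(1 − pf). At p = 10% this runs from 10% when f = 0 down to 0% when f = 1. The document does not allow f to be estimated, so the under-count lies between none and all of the events.

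**The case against.** The strongest reply is that this is a condensed article. It refers to a case registration form, a follow-up proforma, a SPIRIT checklist and a figure with the assessment plan, none of which is shown here. Adverse events may already be recorded on them. That stands: the bare absence of an adverse-event item from the outcome list is not a finding.

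A reader might also infer that harm would leave no trace in the results whatever its true rate. The text does not support that. Replacement is stated, but deletion of data is not. Closed files are kept. The illness clause covers only illness that may hamper the study. Patients who stay in and worsen could show it on NIHSS or Barthel index. No section defines the analysis set, so the exclusion of replaced patients is the natural reading of recruiting to a fixed 20, not a stated rule.

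Nor did the trial promise a safety answer. The word safe describes the treatments being sought in one background sentence, and the phase-I label appears once, in the sample-size paragraph. The objectives concern efficacy, and the design is described as a superiority comparison.

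These points limit the claim but do not remove it. Recording adverse events on a form would not by itself undo a rule that refills the 20 places with people who did not fall ill or quit.

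**Conclusion.** The concern holds in a limited form. The article states a rule that selects against harmed patients, closes the files of those who withdraw, names only efficacy outcomes, and exposes one arm alone to the added regimen. Followed as written, the 20 reached by replacement would under-represent harm in Group B, and the comparison between groups could be biased.

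The size cannot be derived from the document. On the assumed rates of 5% to 20%, and if every event leads to replacement, about 1 to 5 affected Group B patients would be substituted out. The conclusion rests on two assumptions: that results are reported for the patients who fill the 20 places, and that some regimen-related events lead to quitting or to an illness judged to hamper the study. The change should be made, but the point does not stop the trial from going ahead.

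**What to change.** - Name adverse events, serious adverse events and withdrawals with reasons as a stated outcome in Assessment criteria and Variables to be measured.
- Record them on the follow-up proforma through day 90, if they are not already there.
- Amend the data section so that safety data continue to be collected after a patient stops treatment.
- State in Setting that replaced patients stay in the safety report. Give counts with exact two-sided 95% confidence intervals by randomised group. The denominator is everyone who started treatment, including patients who were replaced, so it will exceed 20 in an arm where a replacement brings the number of starters above 20.

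This leaves the regimen and the clinical grounds for stopping as they are. It needs no extra planned visits. The cost is a few more form items, some continued recording for patients who stop, and one descriptive table.

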### Variables to be measured

Improvements in the following assessment variables are expected as primary outcomes: Fugl-Meyer assessment for sensory-motor function of lower extremities, one-leg stance test, functional reach test for static and dynamic balance in patients, quality of life scale and Barthel index independent living of patients with Stroke, resistance experienced during passive range of motion based measured on Modified Ashworth scale NIHSS for improvements in clinical features of stroke are expected to be measured.
^
7
^

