**Aim & Objectives:**

This study compares the adjuvant role of
*Dashmoola Basti* with MRP and FES in stroke recovery. The main goals of this study are to assess and compare the adjuvant role of
*Dashmoola Basti* with standard control over sensorimotor function of lower extremities, static and dynamic balance in stroke patients; gait parameters; resistance experienced during passive range of motion; quality of life of patients; Barthel Index; Modified Ashworth Scale; and Fuglmeyer assessment, Single Limb Stance Test, Functional Reach Test.

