*Dashmoola Basti* with standard control over static and dynamic balance in stroke patients using the Single Limb Stance Test and Functional Reach Test, respectively. The secondary goal is to evaluate and compare the adjuvant role of
*Dashmoola Basti* with standard control over gait parameters (distance and time parameters), the Barthel Index, resistance experienced during passive range of motion based on the modified Ashworth scale, and the National Institute of Health (NIH) stroke-scale-score in stroke patients.

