### Participant timeline

•For physiotherapy (five days weekly for one month)•
*Karma Basti* (alternate regime of
*Niruha Basti* with
*Dashmoola Kwatha* and
*Anuvasana Basti* with
*Dashamoola* oil for complete one month, i.e., Day 1
^st^–Day 30
^th^)

Time schedule of enrolment: Patients with the first Stroke diagnosed with CT/MRI (thrombolytic Stroke only) without other neurological deficits but <6 months of onset will be enrolled for the study.

Interventions (including any run-ins and washouts): There are no washout periods; the intervention of Panchakarma treatment and Physiotherapy sitting for 30 days.

Assessments and visits for participants: Assessment will be carried out at baseline level and after the intervention, i.e., on the 30
^th^ day, then follow-up visits on the 60
^th^ and 90
^th^ day.

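### The Introduction and the Methods contradict each other on which outcomes are primary, and the visible text names no primary visit and no success rule

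*Protocol article*

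**What the plan says.** Three parts of the protocol article describe what the trial is meant to show.

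- **Introduction, closing paragraph.** The study's goal is lower-limb sensorimotor function "in stroke patients using the Fugl-Meyer assessment", together with the comparison "over static and dynamic balance in stroke patients using the Single Limb Stance Test and Functional Reach Test, respectively". A separate sentence begins "The secondary goal is to evaluate and compare the adjuvant role of" Dashmoola Basti and continues "with standard control over gait parameters (distance and time parameters), the Barthel Index, resistance experienced during passive range of motion" on the modified Ashworth scale, and NIHSS. Quality of life is in neither tier.
- **Variables to be measured.** "Improvements in the following assessment variables are expected as primary outcomes" opens a list of Fugl-Meyer, one-leg stance, functional reach, quality of life, Barthel, Modified Ashworth and NIHSS. Gait is absent.
- **Abstract, Aim & Objectives.** "The main goals of this study are to assess and compare the adjuvant role of" the treatment over one unranked list. After sensorimotor function and balance it contains "gait parameters; resistance experienced during passive range of motion; quality of life of patients; Barthel Index; Modified Ashworth Scale", followed by the Fugl-Meyer and balance instruments. NIHSS is absent.

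Participant timeline sets assessments at baseline and day 30, "then follow-up visits on the 60"th and 90th day. Data collection, management, and analysis methods specifies paired and unpaired t-tests. It also gives six instrument-level percentage improvements that will count as significant. It does not rank the outcomes or say how many must succeed. Sample size sets 20 per group on practical grounds, so no calculation there identifies the deciding outcome.

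**The concern.** The primary outcome decides whether a superiority trial has succeeded. Here one section gives an instrument secondary standing and another calls it primary, so no analysis plan could follow both. An unranked list measured at three visits also leaves the deciding result to be chosen after the data are seen. The exposure is greater because the trial is open-label and the investigators who allocate patients also monitor and code the data. A reader of the final report could not tell whether a significant Barthel result at day 90, say, was the planned test or one of many.

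**Working it through.** **1. The lists side by side**

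| Outcome | Abstract, Aim & Objectives | Introduction | Variables to be measured |
|---|---|---|---|
| Fugl-Meyer, lower limb | main | goal | primary |
| Single limb stance | main | goal | primary |
| Functional reach | main | goal | primary |
| Quality of life | main | absent | primary |
| Barthel | main | **secondary** | **primary** |
| Modified Ashworth | main | **secondary** | **primary** (likelier reading) |
| NIHSS | absent | **secondary** | **primary** (likelier reading) |
| Gait | main | secondary | absent |

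The Introduction and the Methods list conflict directly on Barthel under any reading. Modified Ashworth and NIHSS carry a qualifier because the Methods sentence has a second verb at its end, so its closing items could be a separate clause of things to be measured. That leaves five to seven primaries. Seven is likelier: the Abstract's Expected results paragraph names the same seven instruments, though without rank.

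**2. Figures in the plan**

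There is no error rate, alpha or power to reproduce. The calculation below therefore rests on assumptions: each test is two-sided at 5%, and any single significant result could be claimed as success.

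**3. Independent tests**, chance of at least one false positive = 1 − 0.95^k

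- 3 tests (the Introduction's goal, one visit): 1 − 0.95^3 = 14.3%
- 5 tests (narrowest Methods reading, one visit): 1 − 0.95^5 = 22.6%
- 7 tests (one visit): 1 − 0.95^7 = 30.2%
- 5 × 3 = 15 tests: 1 − 0.95^15 = 53.7%
- 7 × 3 = 21 tests: 1 − 0.95^21 = 65.9%

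**4. Correlated tests.** Simulation of 20,000 null trials, 20 per arm, unpaired t-tests, seven instruments. The correlations are assumed, because the article gives none.

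| Correlation between outcomes | One visit | Three visits, between-visit r 0.5 | Three visits, r 0.7 | Three visits, r 0.9 |
|---|---|---|---|---|
| 0 | 30.1% | 61.8% | 55.6% | 46.4% |
| 0.3 | 26.7% | 56.5% | 51.4% | 42.4% |
| 0.5 | 23.0% | 50.0% | 44.0% | 35.8% |
| 0.7 | 17.7% | 40.2% | 36.1% | 28.2% |
| 0.9 | 11.3% | 27.1% | 23.4% | 18.6% |

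With the independent case added, the range is about 11–30% at one visit and 19–66% over three visits.

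**5. False results favouring the added treatment only** (nominal 2.5% per test)

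- One visit, independent: 1 − 0.975^7 = 16.2%; at correlation 0.9 the simulation gives 5.5%.
- Three visits, simulated: 9.2% (both correlations 0.9) to 37.2% (outcomes uncorrelated, visits 0.5). Full independence, which repeated measures on one patient would not show, gives 1 − 0.975^21 = 41.2%.

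**6. After repair**

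One outcome at one visit returns the rate to 5%. Keeping seven at one visit under Bonferroni means 0.05/7 = 0.0071 per test; keeping all 21 means 0.05/21 = 0.0024.

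**The case against.** Several points on the other side are sound and limit the claim.

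- A reader might infer three rival primary sets. Only Variables to be measured uses the word primary. The Abstract's list can be read as a condensation that merges the Introduction's two tiers and adds quality of life. It matches neither other list, but the firm contradiction is between two places.
- A reader might take seven primaries as certain. The run-on sentence permits five to seven.
- A reader might take all 21 comparisons as equally eligible. Participant timeline separates the day-30 assessment from the later follow-up visits, which hints that day 30 is the main one without saying so. Figure 1, which covers the assessment plan, is not available here, so the absence of a primary visit is established only for the visible text.
- A reader might take a false-positive rate several times 5% as a property of the trial. It depends on an unstated alpha, assumed correlations and an any-one-wins rule. If all seven had to be significant, there would be no inflation; the article states neither rule. At one visit with correlation 0.9 the rate is only about twice 5%. The two-sided figures also overstate the chance of a falsely favourable result.
- Multiplicity handling is often left to an analysis plan, and Sample size calls this a phase-I trial.

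The last point does not remove the problem. Condensing a protocol explains omissions, not one instrument placed in two tiers. The Study design section declares superiority, which needs a deciding outcome whatever the phase label.

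**Conclusion.** The point holds as a contradiction between the Introduction and Variables to be measured. It is certain for Barthel and likely for Modified Ashworth and NIHSS. Gait is secondary in one and missing from the other's primary list; quality of life is primary in one and missing from the other's goals. This part needs no assumption about alpha or correlation.

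The size is conditional on two-sided 5% tests, seven instruments and freedom to claim any one result: about 11–30% at one visit and 19–66% over three, or about 9–37% over three visits for results favouring the added treatment. These figures show what the wording permits. They do not show that outcomes will be selected.

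It should be settled before outcome data are analysed, because the trial's conclusion depends on it and the repair is cheap.

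**What to change.** Before outcome data are analysed:

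1. Name one primary outcome at one visit, judged by the between-group comparison and not by paired within-group tests. Lower-extremity Fugl-Meyer at day 30 is a natural choice: it comes first in the Introduction, Assessment criteria, Variables to be measured and the improvement thresholds, and day 30 is the end of treatment. In the Abstract's objectives only its construct comes first; the instrument is named later.
2. Make all other outcomes, gait included, and all day-60 and day-90 results secondary, reported with estimates and confidence intervals. If several primaries are preferred, list them and state an error-controlling rule such as Holm.
3. Use the same list and ranking in the Abstract, Introduction, Assessment criteria, Variables to be measured and the analysis section.
4. State that the percentage-improvement thresholds do not define statistical significance.

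The cost is protocol and registry wording. The downside is that fewer outcomes can carry the headline claim.
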